## Abstract

**Background:**

Providing care in Kenya to all youth in need is difficult because of a shortage of professional providers and societal stigma. Previous trials of the Anansi model, which involves delivering low-touch mental health interventions through a tiered caregiving model (including lay-providers, supervisors, and clinical experts), have shown its effectiveness for reducing depression and anxiety symptoms in school-going Kenyan adolescents. In this trial, we aim to assess two different scale-up strategies by comparing centralized implementation (i.e., by the organization that designed the Anansi model) against implementation through an implementing partner.

**Methods:**

In this three-arm trial, 1600 adolescents aged 13 to 20 years will be randomized to receive the Shamiri intervention from either the Shamiri Institute or an implementation partner or to be placed in the treatment as usual (TAU) control group. The implementation partner will be trained and supplied with protocols to ensure that the same procedures are followed by both implementors. Implementation activities will run concurrently for both implementors. The Shamiri intervention will be delivered by trained lay providers to groups of 10–15 adolescents over four weekly sessions which will take place in secondary schools in Machakos and Makueni counties in Kenya. The TAU group will receive the usual care offered by their respective schools. Outcomes will be assessed at baseline, midpoint (2 weeks), endpoint (4 weeks), and 1 month follow-up. The analysis will be based on an intent-to-treat approach. Mixed effects models will be used to assess trajectories over time of the primary outcomes (anxiety and depressive symptoms, mental well-being, perceived social support, and academic performance) and secondary outcomes for the intervention groups and the control group. Effect sizes will be computed for the mean differences of the intervention and control arms at midpoint, endpoint, and follow-up.

**Discussion:**

This trial will provide insight into the comparative effectiveness of different strategies for scaling a school-based mental health care model. Findings will also indicate areas for improved efficiency of the model to enhance its replicability by other implementors.

**Trial registration:**

Pan African Clinical Trials Registry (PACTR) (ID: PACTR202305589854478, Approved: 02/05/2023).

**Supplementary Information:**

The online version contains supplementary material available at 10.1186/s13063-023-07539-y.

## Administrative information

Note: The numbers in curly brackets in this protocol refer to SPIRIT checklist item numbers. The order of the items has been modified to group related items (see http://www.equator-network.org/reporting-guidelines/spirit-2013-statement-defining-standard-protocol-itemsfor-clinical-trials/).

## Introduction

### Background and rationale {6a}

Mental disorders remain severely undertreated around the world. The World Health Organization (WHO) highlights that mental disorders are widely misunderstood, underfunded, and under-resourced in all countries and more severely so in low- and middle-income countries (LMICs) [1, 2]. Due to inadequate treatment, mental disorders are the second leading global cause of disability [3]. From 1990 to 2019, the global disability-adjusted life years (DALYs) burden attributed to mental disorders increased by 58.1% to 125.3 million [4].

Increased symptoms of anxiety and depression are highly prevalent among adolescents in Sub-Saharan Africa (SSA) [2, 5]. Early identification and treatment of mental disorders are critical to prevent risky behaviors, social and health risks, and over-institutionalization [2, 6]. However, limited access to mental health care in these regions hinders young people’s ability to lead healthy and fulfilling lives [5]. The scarcity of trained mental healthcare providers, lack of mental health resources, societal stigma, and lack of culturally appropriate interventions are barriers young people in SSA face to accessing mental health services [7–10]. Therefore, there is a need to develop and evaluate scalable and low-cost mental health interventions.

To address this gap, researchers have tested several mental health interventions for youth living in low- and middle-income countries [11], including the Shamiri Intervention, a brief character strengths intervention that has been tested in several trials [10]. The Shamiri (Swahili for “thrive”) intervention [8, 12, 13] was designed to improve mental health and wellbeing by shifting young people’s perceptions of themselves and their world. It is administered by lay providers in four hourly sessions across four weeks and consists of three modules: growth mindset, value affirmations, and gratitude [6, 14, 15]. The intervention has demonstrated promising outcomes in enhancing academic performance, psychosocial well-being, and mental health among adolescents. These results add to the growing body of literature on brief low-touch interventions for youth mental health outcomes [15, 16].

The initial randomized controlled trial of the Shamiri intervention was implemented among school-going Kenyan youths with elevated depression and anxiety symptoms (*n* = 51). Compared to an active study skills control group, the intervention significantly improved participants’ depressive and anxiety symptoms, perceived social support, and academic performance [12]. These findings were replicated in a pre-registered study with a larger sample of participants (*n* = 413) with the intervention’s effects persisting at the 7-month follow-up [8]. The development and evaluation of the Shamiri intervention demonstrate the potential for character strength interventions to improve the mental health, academic, and social outcomes of Kenyan youth.

A question that emerges is how do we scale up these types of interventions to address the youth mental health treatment gap? One way of doing this is developing strategies that can allow for these light-touch, school-based interventions, like the Shamiri intervention, to be delivered through possibly scalable models. Our team sought to develop such a model for the delivery and scaling of the Shamiri intervention. The model that we developed was a three-tier caregiving model consisting of mental health workers with varying levels of training [17]. At the first tier of the model are lay providers; recent high school graduates who receive training to lead group sessions. The second tier consists of clinical supervisors who have some mental health experience (e.g., a bachelor’s degree in psychology) and are further trained through a 7-week program that covers topics including supervision and support for lay providers, handling clinical emergencies, providing one-on-one support to students, and referring participants to the third (expert) tier of the model when necessary. The third tier is composed of a clinical network of Kenyan mental health experts, most with doctoral degrees in psychology or psychiatry [12, 17]. This model, which is sometimes referred to as the “Anansi” model, allows for the expansion of the caregiving supply by mobilizing an expanded array of caregivers and offers opportunities for clinical escalation and triaging [18]. Over the past 3 years, more than 9500 youths have received the Shamiri intervention through the Anansi model, demonstrating the model’s scalability [19, 20].

We use two ways of scaling up mental healthcare models. The first, which we call a “centralized approach,” involves an organization ramping up its internal capabilities to increase the reach of its model. In this approach, scale-up is done entirely by the organization through which an intervention is developed. The second approach, which we call a “decentralized” approach (and is sometimes also called a “train-the-trainers” approach), involves an organization training other third-party organizations to replicate its own model.

This study builds on the promising findings on the Shamiri intervention and tests the two possible pathways of scaling up the Shamiri intervention. Particularly, we aim to evaluate whether implementation of the Shamiri intervention through the Anansi model retains its effectiveness in improving youth psychological, social, and academic outcomes when implemented at scale by an external partner through the decentralized scale-up model. Additionally, this trial will shed light on the strengths and limitations of the Anansi model for scaling up.

### Objectives {7}

The primary objective of this study is to explore ways of scaling the Shamiri intervention through the Anansi model in Kenyan secondary schools. We will realize this aim through two specific objectives. First, this study will test the effectiveness of the Anansi model in school settings through a large-scale dissemination study with 1600 adolescents. We hypothesize that the Shamiri intervention will positively influence adolescent’s psychological, social, and academic outcomes when delivered through the Anansi model. The second objective is to compare two strategies of scaling the Shamiri intervention through Anansi in Kenya, either implemented by the Shamiri Institute or by a community-based partner. We hypothesize that the intervention run by the community-based partner will be equally effective as the one carried out by the Shamiri Institute.

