## Interventions

### Explanation for the choice of comparators {6b}

The primary objective of this trial is to compare a centralized vs decentralized approach to scaling, assessing the comparative effectiveness of each approach. To achieve this, the Shamiri-Institute-delivered intervention (centralized) will be compared against the Shamiri Intervention delivered by the implementing partner (decentralized). A treatment as usual control group is included to provide a practical reference point from which the intervention’s efficacy for both implementors will be estimated relative to what school-going adolescents would typically receive.

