### Sample size {14}

We used the *simr* package in R to estimate the sample size needed for this trial. We used the lowest standardized effect size between the intervention and control we observed in a prior study [8] as our target effects, which was 0.22. Power simulations revealed that to detect an effect size of at least 0.22 at any time point with a significance level of *α* = 0.05 and a power of at least 80%, an effective sample size (i.e., including attrition of 40%) of 1554 participants is required. We expect up to 30% attrition at the midpoint and endpoint and up to 40% by follow-up based on our past trial [8], which is high. We rounded this up to 1600 participants required at baseline. For more details on our sample size determination and power analysis procedure, please see the supplementary materials.

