Gender will be included because Kenyan adolescents have shown gender differences in internalizing problems [8, 12]. Female adolescents have previously reported higher anxiety and depression symptoms as compared to males. Past studies [8, 12] have shown that adolescents in lower-resource schools report higher depression and anxiety symptoms. Lastly, we will include details of lay providers like gender because we would like to explore if the gender of a lay provider affects the study participants.

A *p*-value less than 0.05 in the interaction between the time variable and the arm variable will be considered statistically significant. If the interaction is significant, we will look at the conditional mean difference between the arms at each time point from end point to follow-up. We will assess this and report marginal (predictive) means. If these differences are significant (*p* < 0.05) and the control has scores associated with less favorable outcomes, we will conclude there was improvement due to centralized or decentralized arm over time. If the interaction is not significant but the main effect of centralized or decentralized arm is, and the effect points to lower symptoms in the centralized or decentralized arms, we conclude there was improvement due to centralized or decentralized delivery.

Effect sizes (ESs) will be computed from the mean differences across the different time points for the arms. We will compare Cohen’s D for each outcome at baseline, midpoint, endpoint, and 1-month follow-up for the study participants in the Shamiri intervention arms and TAU control arm. Statistically significant Cohen’s *D* in the direction of less symptoms on average in the arms will reflect greater improvements for intervention compared to control.

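### The hypothesis that partner delivery is as effective as Institute delivery has no margin and no decision rule, and the stated sample size was not set for it

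*Protocol article*

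**What the plan says.** **Hypothesis.** Objectives {7}: "We hypothesize that the intervention run by the community-based partner will be equally effective as the one carried out by the Shamiri Institute".

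**Rank of the comparison.** Two sections differ. Explanation for the choice of comparators {6b} says: "The primary objective of this trial is to compare a centralized vs decentralized approach to scaling, assessing the comparative effectiveness of each approach". Objectives {7} puts it second: "The second objective is to compare two strategies of scaling the Shamiri intervention through Anansi in Kenya".

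**Sample size {14}.** The target is the "lowest standardized effect size between the intervention and control we observed in a prior study [8] as our target effects, which was 0.22", "with a significance level of *α* = 0.05 and a power of at least 80"%. The result is 1554 including 40% attrition, rounded up to 1600. Attrition of up to 30% is expected at midpoint and endpoint, and up to 40% by follow-up.

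**Decision rules {20a}.** If the arm-by-time interaction has p < 0.05, the arms are compared at each time point from endpoint to follow-up. Where the differences are significant and control does worse, "we will conclude there was improvement due to centralized or decentralized arm over time". If the interaction is not significant but an active arm's main effect is, and it points to lower symptoms, the conclusion is again improvement from that delivery. Cohen's D is interpreted as intervention against control.

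**Intended use.** The Discussion says that showing the intervention keeps its utility whoever implements it would support scale-up through a partner.

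**The concern.** A claim of sameness needs a stated amount of loss that would still count as the same, and a rule saying when the data exclude a larger loss. The protocol has neither, and its p < 0.05 rules are built to show improvement over control. With only those rules, an analyst who wants to report on the hypothesis has two obvious substitutes. One is to take a non-significant difference between the active arms as equality. The other is to compare which arms reached significance against treatment as usual (TAU). Neither is valid.

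At stake is the scale-up message. Partner delivery could be called as good as Institute delivery after losing much of the effect, or called different when the two are truly the same.

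**Working it through.** **Inputs from the protocol:** 1600 randomized; attrition 30% at endpoint and 40% at follow-up; target effect 0.22 SD; α = 0.05; groups of 10 to 15; equal allocation intended.

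**Assumptions (not in the protocol):** 1:1:1 allocation, SD = 1, two-sided test, midpoint group size 12.5 shrinking with attrition, group ICC 0 to 0.05, no baseline adjustment, and a true difference of zero for non-inferiority power.

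**1. The plan's own figure.** For two arms, d = 0.22, 80% power and two-sided 0.05, n = 325 per arm. Three arms give 975, and 975 / 0.6 = 1625, against the stated 1554. At 1600 with 40% attrition (320 per arm), power against TAU is 79.5%. The stated figure comes from a mixed-model simulation whose details are in a supplement, so exact agreement is not expected and the figure is not called wrong. The effect it targets is active versus control.

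**2. Precision of decentralized minus centralized.**
- n per arm: 1600 × 0.7 / 3 = 373 at endpoint; 1600 × 0.6 / 3 = 320 at follow-up.
- Design effect: DE = 1 + (m − 1) × ICC. At ICC 0.05, endpoint m = 12.5 × 0.7 = 8.75 and DE = 1.3875; follow-up m = 12.5 × 0.6 = 7.5 and DE = 1.325.
- SE = √(2 × DE / n); half-width = 1.96 × SE.

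| | ICC | SE | 95% half-width | Share of 0.22 |
|---|---|---|---|---|
| Endpoint | 0 | 0.073 | 0.143 | 65% |
| Endpoint | 0.05 | 0.086 | 0.169 | 77% |
| Follow-up | 0 | 0.079 | 0.155 | 70% |
| Follow-up | 0.05 | 0.091 | 0.178 | 81% |

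**3. Chance of a non-significant difference between the active arms,** for true difference δ: 1 − Φ(δ/SE − 1.96) − Φ(−δ/SE − 1.96).
- Partner loses half the effect (δ = 0.11): 68% to 75% at endpoint, 71% to 77% at follow-up.
- Partner loses all of it (δ = 0.22): 15% to 28% at endpoint, 21% to 32% at follow-up.

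**4. Non-inferiority power** for margin M: Φ(M/SE − 1.96). At endpoint, from ICC 0.05 to ICC 0:
- M = 0.11: 25% to 32%.
- M = 0.22: 72% to 85%. This margin would allow the whole target effect to be lost.

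**5. Comparing significance against TAU.** Suppose both active arms truly have d = 0.22. The two tests share the TAU arm, so their correlation is 0.5. Exactly one arm is then significant in 18% (endpoint) to 23% (follow-up) of trials at ICC 0, and in 27% to 30% at ICC 0.05. Differing significance is therefore no evidence that the implementers differ.

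**The case against.** **The contrast is already available.** Section {20a} fits one mixed model to both Shamiri arms and TAU, and reports marginal means and differences between arms. The partner-minus-Institute estimate and its CI follow from it. This stands: a criterion is missing, not an analysis. A reader might infer that the comparison cannot be answered at all, but the document does not support that.

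**It may not be the primary comparison.** A reader might take it as such from {6b}, but {7} ranks it second. This also stands. The gap exists under either ranking, and the conflict needs reconciling.

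**The protocol never says that non-significance will be read as equality.** Correct. The Discussion could also be read as each arm beating TAU, for which rules exist. But the Objectives section predicts equal effectiveness, which goes further than both arms beating control.

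**A margin could sit in a statistical analysis plan or supplement.** It could. But the protocol itself fixes the hypothesis, the effect used for sizing and the conclusion rules, and the last two do not serve the first.

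**The arithmetic is simpler than the planned model.** True. Baseline scores may be included. With an assumed baseline-outcome correlation of 0.5 to 0.7 and ICC 0, the endpoint chance of non-significance at δ = 0.11 falls to 59% to 44%, and non-inferiority power at 0.11 rises to 41% to 56%. Also, 0.22 is the lowest effect in the prior study, so outcomes with larger effects would fare better. Even so, power at half the target effect stays below 60%.

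**Conclusion.** The concern holds as a mismatch between a stated hypothesis and the stated rules and sizing. Nothing in the document could confirm equal effectiveness of the two implementers. The data expected would give a 95% CI half-width of about 0.14 to 0.17 SD at endpoint and 0.15 to 0.18 SD at follow-up, roughly 65% to 80% of the 0.22 SD target effect. These figures are unadjusted approximations and rest on 1:1:1 allocation, SD 1 and an assumed group ICC of 0 to 0.05. Baseline adjustment would narrow the interval.

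It does not follow that the sponsor plans to treat p > 0.05 as proof of equality. Nor does it follow that the contrast belongs only to depression and anxiety at endpoint: the protocol names five primary outcomes, and its rule runs from endpoint to follow-up.

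**What to change.** Recruitment is reported as complete, so this is a change of wording and analysis, to be made before the arms are compared. Choose one:

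- **(a) A confirmatory contrast.** Prespecify decentralized minus centralized from the planned mixed model, on the primary outcome(s) and time point that the sponsor names. Give a justified margin, for example as the share of the 0.22 SD effect that must be kept. Conclude that partner delivery is not worse only if the 95% CI excludes that margin, and state the power for it.
- **(b) Estimation.** Restate the objective as estimating the difference with a 95% CI, and remove the claim of equal effectiveness.

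In both cases, state that p > 0.05 between the active arms will not be read as equality. State also that one arm being significant against TAU and the other not will not be read as a difference. Reconcile {6b} and {7} on the rank of this objective.

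Cost: protocol or analysis-plan wording and, under (a), one contrast from a model already planned. The stated power for this objective will look less favourable. No extra participants are needed.

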### Trial design {8}

To assess the effectiveness of two different approaches for scaling the Anansi model of tiered lay psychotherapy, we will conduct a three-arm randomized controlled trial in seven Kenyan secondary schools. The Shamiri Institute team will partner with a community-based implementing partner, Africa Mental Health Research and Training Foundation (AMHRTF), to trial the Anansi care-giving model as an after-school program. We will train the implementation partner and provide them with a manual and protocol to ensure that both parties follow the same implementation procedures. The partner will implement the intervention in parallel with the Shamiri Institute.

Throughout this protocol, the delivery of the Shamiri intervention by the Shamiri Institute is referred to as the centralized approach whereas delivery of Shamiri intervention through the implementing partner is referred to as the decentralized approach. To compare the effectiveness of the centralized and decentralized approaches, participants will be randomized to receive the Shamiri intervention either through the Shamiri Institute or the community-based implementing partner or be randomized to a treatment as usual (TAU) control group.

## Methods: participants, interventions, and outcomes

### Study setting {9}

This study will be conducted in seven high schools across two out of the forty-seven Kenyan counties, namely Makueni and Machakos. Makueni County has a population of around 990 thousand, while Machakos County has about 1.4 million [18]. The study team has extensive experience working with schools in the targeted counties [8, 21]. In Kenya, the Ministry of Education categorizes high schools in three broad categories: private, Harambee, and state-owned schools. Private schools are funded by individuals or private organizations, Harambee schools are built and funded by the community, and state-owned schools are funded by the government. The schools are further classified as either national, extra-county, county, or sub-county schools—and as day, boarding, girls only, boys only, or mixed-gender [21].

National schools are for students with particularly high-test scores, while extra-county schools are ranked after national schools. Students who do not qualify for these schools may be placed in county schools, which are ranked higher than sub-county schools. We aim to include a diverse set of schools that represent the nature of schools in Kenya while prioritizing adolescents in lower-resource settings (e.g., prioritizing public over private schools) since the Shamiri intervention is primarily aimed to be used in a lower-resource setting.

